### Sample Size

The calculation formula for the sample size used in this study will follow the methodology described by O’Neill [29]. Assuming vaccination coverage between 20%-90%, a precision of ±5%, a type 1 error rate of 0.05, and an anticipated VE of 50%-90%, the minimum sample size needed for each specific COVID-19 vaccine brand and dose VE analysis is roughly around 15,000, with 5000 cases and 10,000 controls [24,29] (Table S4 in Multimedia Appendix 1).

We expect to analyze 400,000-900,000 people after the aggregation of all datasets. Therefore, we should have enough data to conduct the VE analyses for each specific COVID-19 brand and regimen in our final dataset. We will compare the proportion of COVID-19 vaccines received by eligible people in our dataset during each period of interest to those reported by the Ministry of Health [17] (Table S1 in Multimedia Appendix 1). Furthermore, we will exclude people who received COVID-19 vaccine brands with vaccination coverage of less than 20%, as these vaccines are usually distributed briefly in the population or only available to specific subgroups within the community. Moreover, we might consider combining different COVID-19 vaccine brands with the same platform into one group to decrease the required sample size, especially for the subgroup VE analysis [24].

### Statistical Analysis

We adopted our VE analysis from the Interim Guidance of Evaluation of COVID-19 Vaccine Effectiveness by the World Health Organization, where the final estimate of absolute VE (aVE) will be determined by calculating the adjusted odds ratio (aOR) for vaccination using the formula aVE = (1 – aOR) × 100% [24]. Unconditional multivariable logistic regression will be used to analyze the aOR of having symptomatic and fatal SARS-CoV-2 infection between the unvaccinated and vaccinated participants. We will perform separate analyses for the Delta- and Omicron-dominant periods. Furthermore, within each period, we will also analyze each vaccinated person separately by their vaccine brand or platform and vaccination doses, such as dose 1, dose 2, or booster. For the main aVE analyses, we will include only vaccinated people with the last dose 1 or dose 2 vaccination date within 14-90 days or with the last booster dose within 7-90 days before their index test date and compare them to the unvaccinated people.

One main logistic model will be assembled by forward inclusion, and only covariates with less than 20% missing data will be considered to be included in the model building. Assessment for confounders and effect modifiers will be performed with the Wald test and by observing the change in the primary exposure coefficient SE. Covariates that act as confounders will be included in the model. If effect modification is present, it is essential to report VE and CIs for each subgroup individually. The linearity between continuous variables and the log odds of having symptomatic SARS-CoV-2 infection will be assessed, and the continuous variables will be modified into categorical variables if necessary. The overall fit of the final multivariate logistic regression model will be assessed with Hosmer and Lemeshow goodness-of-fit test [30], as matching might incur matching-related bias from the cases and controls having similar exposure, thus underestimating the aVE. We will also perform conditional logistic regression as a sensitivity analysis for measuring the aVE estimation against symptomatic SARS-CoV-2 infection or our primary objectives [31,32]. Furthermore, for the analysis of the Omicron period, we will perform an additional analysis of relative VE (rVE) by comparing recipients of one booster dose to recipients of the 2 doses who were eligible to receive the booster dose. The rVE will be calculated using the formula rVE = [(aVE from booster dose – aVE from 2 doses and eligible for booster)/(1 – aVE from 2 doses and eligible for booster)] × 100%. For the rVE analyses, we will include only people whose last booster dose was within 7 to 90 days before their index test date and compare them to people whose last 2-dose vaccination date was ≥90 days before their index test date [24].

This study will also conduct subgroup analyses based on the time between the last vaccination date and test index date to assess for waning of immunity (Table 2). These subgroup analyses will be conducted separately for each wave and vaccine brands or regimens. Similar to the main analysis, each vaccinated subgroup will be compared to unvaccinated people.

**Table 2 table2:** Subgroup analysis based on time since last vaccination.

Subgroup	Description
1	7-14 days between the last vaccination dose and index test date
2	14-28 days between the last vaccination dose and index test date
3	28-56 days between the last vaccination dose and index test date
4	56-90 days between the last vaccination dose and index test date
5	90-180 days between the last vaccination dose and index test date
6	>180 days between the last vaccination dose and index test date

A 2-sided *P* value derived from the multivariable logistic regression analysis will be used to assess VE. Data linkage and data cleaning will be performed in Google Collaboratory with the Python programming language. Furthermore, the Statsmodel library package will be used for statistical analysis [33].

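### VE against 30-day death relies on the same ordinary logistic fit as symptomatic infection, and that fit breaks down in any cell with no vaccinated deaths

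*Protocol article*

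**What the plan says.** The Statistical Analysis section of the protocol article sets one model for both outcomes: "Unconditional multivariable logistic regression will be used to analyze the aOR of having symptomatic and fatal SARS-CoV-2 infection". Within each wave the plan will "analyze each vaccinated person separately by their vaccine brand or platform and vaccination doses, such as dose 1, dose 2, or booster". The main contrasts restrict the vaccinated group by timing ("last dose 1 or dose 2 vaccination date within 14-90 days or with the last booster dose within 7-90 days"), counted back from the index test, and compare it with the unvaccinated. VE is judged by a two-sided P value from that regression, and "the Statsmodel library package will be used for statistical analysis". The one alternative model, conditional logistic regression, is a sensitivity analysis for symptomatic infection only.

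The Sample Size section puts the minimum for each brand-and-dose analysis at "roughly around 15,000, with 5000 cases and 10,000 controls", for coverage of 20% to 90%, VE of 50% to 90%, precision of ±5% and "a type 1 error rate of 0.05". It gives no number of deaths and no case fatality. It then expects 400,000 to 900,000 people in all, which it regards as sufficient for each brand and regimen. Brands below 20% coverage are excluded, and brands of one platform may be combined. VE against 30-day mortality is a stated secondary objective.

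**The concern.** Symptomatic infection and death differ greatly in frequency. A size of 5,000 cases supports the first outcome, but the information on death depends on how many of those cases died and how many of the dead were vaccinated. Where a vaccine works well and few people in the contrast received it, that last number can be zero. The odds ratio estimate is then zero, its logarithm has no finite value, and the standard error reported by the software means nothing.

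The P value is what is at stake. A Wald P divides the coefficient by its standard error. In a zero cell the standard error grows far faster than the coefficient, so P moves towards 1 just when the data favour the vaccine most. Such a cell becomes more likely as VE rises, so the failures would not fall at random across vaccines.

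**Working it through.** **Inputs from the documents.** 5,000 cases and 10,000 controls; coverage c of 20% to 90%; VE of 50% to 90%, not given separately for death; expected total of 400,000 to 900,000 people.

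**Assumptions.** Case fatality is not in the documents, so a range is shown. Deaths are compared with test-negative controls. Calculations are crude 2×2; covariate adjustment would make sparse cells sparser. Maximum likelihood and Wald inference are inferred from the model name and the software; the text does not name them.

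**1. The plan's own size.** Share of cases vaccinated: p1 = c·OR / (1 − c + c·OR), with OR = 1 − VE. Cases needed = [1/(p1(1 − p1)) + 1/(2c(1 − c))] × (1.96·OR/0.05)². At VE 50% and coverage 20%, p1 = 0.10/0.90 = 0.1111, so cases = 13.25 × 19.6² = 5,090 and the total is 15,270. This reproduces the stated 5,000 and 15,000, and the formula concerns cases only.

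**2. Vaccinated deaths at that size.** At VE 90% and coverage 20%, p1 = 0.02/0.82 = 2.44%. With D deaths, the expected number vaccinated is D × p1 and the chance of none is (1 − p1)^D.

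| Assumed fatality | Deaths D | Expected vaccinated deaths | Chance of none |
|---|---|---|---|
| 0.3% | 15 | 0.37 | 69% |
| 1% | 50 | 1.2 | 29% |
| 2% | 100 | 2.4 | 8.5% |
| 3% | 150 | 3.7 | 2.5% |

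**3. How far this extends.**
- VE 80%, coverage 20%, 50 deaths: chance of none 8.7%.
- VE 50%, coverage 20%, 50 deaths: 5.6 expected, chance of none 0.3%.
- VE 90%, coverage 50%, 50 deaths: chance of none 0.9%.
- VE 90%, coverage 90%, 50 deaths: 23.7 expected, chance of none about 0.
- Larger size, assuming about 67,000 cases per wave (400,000/3/2) in one contrast, with VE 90% and coverage 20%: at 1% fatality 16.3 expected and chance of none about 0; at 0.1% fatality 1.6 expected and chance of none 19%.
- Small cell, assuming 500 deaths (50,000 cases at 1%) and a vaccinated group that is 5% of its contrast: p1 = 0.005/0.955 = 0.52%, 2.6 expected, chance of none 7%.

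**4. What the fit reports in a zero cell.** Take 50 deaths, none vaccinated, and 10,000 controls of whom 2,000 are vaccinated.
- Statsmodels Logit: not converged, coefficient −19.4, SE about 4,515, Wald P = 0.997.
- Likelihood ratio: the log-likelihood is 50 ln(50/8050) + 8000 ln(8000/8050) = −303.91 with a vaccine effect and 50 ln(50/10050) + 10000 ln(10000/10050) = −315.04 without. Twice the difference is about 22.25 on 1 degree of freedom, P about 0.000002.
- Firth estimate (0.5 added to each cell in this saturated table): OR = (0.5/2000.5)/(50.5/8000.5) = 0.040, so VE is about 96%.

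**5. What happens with one or more vaccinated deaths.** The ordinary fit converges (SE 1.01 with one, 0.72 with two). Wald 95% coverage given at least one vaccinated death (VE 90%, coverage 20%) is 84% at 15 total deaths, 95.1% at 25, 95.3% at 50, 96.1% at 100 and 96.8% at 150. The intervals are wide: at 50 deaths the median runs from about 38% to 99%. If undefined intervals count as misses, coverage at 50, 100 and 150 deaths is 68%, 88% and 94%, against 97%, 96% and 94% for Firth with profile-likelihood limits. From 50 deaths up, that shortfall comes from the zero cells.

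**The case against.** The strongest reply is that logistic regression is standard for a test-negative design, and that a fallback for sparse cells is the kind of detail a full protocol or SAP would hold. Neither is shown, so the absence of a fallback is not in itself an error. That stands. But the article does not leave the method open: it names the model for the fatal outcome, the source of the P value and the software, and followed as written these can mislead in a zero cell.

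It is also true that 15,000 is a minimum, that far more people are expected, that brands below 20% coverage are excluded and that platform analysis is allowed. These limit the problem considerably. They do not remove it, because the 20% screen applies to brands and not to a dose or a 14–90-day window within a brand.

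A reader might infer more than the documents support:
- **That Wald intervals are unreliable whenever vaccinated deaths are few.** Step 5 shows near-nominal coverage from about 25 total deaths up, once one vaccinated death has occurred.
- **That every brand-dose cell is affected.** Step 3 confines the risk to high VE combined with low coverage, and to small or low-fatality cells.
- **That death will also be split by time since dose.** The text says "These subgroup analyses will be conducted separately for each wave and vaccine brands or regimens", but does not name the fatal outcome there, and the objectives list mortality and time since dose separately.
- **That the plan bases its VE intervals on Wald tests.** The sentence "Assessment for confounders and effect modifiers will be performed with the Wald test" concerns model building.
- **That failed cells would be dropped, to the disadvantage of the best vaccine.** Nothing in the article says so.

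**Conclusion.** The point holds in a narrow form. The stated analysis of VE against death has no valid result for a cell without vaccinated deaths, and its P value there can point the wrong way. At the minimum size with 20% coverage and VE 90%, the chance of such a cell runs from about 69% to 2.5% as assumed fatality runs from 0.3% to 3%. At higher coverage, at VE 50%, or at the full expected size with fatality near 1%, it is close to nil. It returns at about 7% per cell where the vaccinated group is 5% of a contrast with 500 deaths.

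These figures rest on assumed fatality, on the upper end of the plan's VE range applying to death, on crude tables, and on reading the planned model as ordinary maximum likelihood with Wald P values. The symptomatic analysis is not affected.

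**What to change.** For the fatal-outcome contrasts, specify Firth-penalised logistic regression with profile-likelihood 95% confidence intervals and P values. Report every prespecified cell with its count of vaccinated deaths, including cells where the count is zero.

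Do not make pooling of brands depend on the observed number of vaccinated deaths. Such a rule depends on the outcome and would merge away the brands with the highest VE; the penalised fit gives finite estimates without it. If platforms are to be used, choose them on grounds that do not involve the deaths.

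The article's Results section says analysis is under way, so this should be fixed before the fatal-outcome cells are examined, or the timing disclosed if they have been. The cost is a sentence of text, a short extra routine and slight shrinkage in sparse cells. Where deaths are plentiful the results barely change.

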### Study Participants

The study will include people 18 years or older who domiciled in Jakarta and underwent an RT-PCR test for SARS-CoV-2 infection due to symptoms of influenza-like illnesses within 10 days of the test date. Although people may have more than one RT-PCR result during the period of interest, this study will only account for the first positive or negative result per person as the index test date for each of the COVID-19 waves. People who had at least one sample with a positive SARS-CoV-2 RT-PCR result during the period of interest will be classified as cases, while people with a negative SARS-CoV-2 RT-PCR without any positive results over the period of interest will be classified as controls.

People with a positive RT-PCR test result within 90 days of the preceding index test date, with inconclusive RT-PCR results, who received different vaccines for dose 1 and dose 2 or a heterologous primary vaccine series, or who had a time interval between dose 1 and dose 2 that was less than the government recommendation (<21 days for Pfizer and Sinopharm, <28 days for CoronaVac and Moderna, and <12 weeks AstraZeneca) will be excluded from the analysis. We will also exclude people with incomplete vaccination records, such as people who declared receiving 2 vaccine doses without being able to verify the previous dose.

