### Study Variables

The primary outcome in this study is symptomatic SARS-CoV-2 infection, defined as a positive RT-PCR test within 10 days from the onset of influenza-like illness. The secondary outcome in this study is fatal SARS-CoV-2 infection, defined as death within 30 days after a positive RT-PCR test result [24]. Meanwhile, the primary exposure in this study was vaccination status, which can be classified as unvaccinated, dose 1 or partial vaccination, dose 2 or primary vaccination, and booster dose. People without any vaccination entries after data linkage with the PCARE Vaksin dataset at the end of each period of interest will be classified as unvaccinated persons. For vaccinated people, we will only consider the last vaccination data entry that happened before the patients’ index RT-PCR test date.

Several covariates should be assessed as potential confounders in the study, such as age in years at the index test date, gender, calendar week of the RT-PCR collection during the period of interest, living in impoverished neighborhoods, presence of any comorbidities, occupation, and reinfection status. The calendar week of the RT-PCR collection during the period of interest will be presented as a whole number starting from week 1 as the start of the period of interest. Living in an impoverished neighborhood will be presented as a dichotomous variable. People will be classified as living in an impoverished neighborhood if their neighborhood number at the subdistrict level is listed as one of the impoverished neighborhoods in the 2018 Jakarta Governor’s regulation concerning improving the quality of settlements in residential areas. Occupation will be presented as categorical variables that consist of health care worker, public or government official, and civilian. Reinfection or people with previous SARS-CoV-2 infections will be presented as a dichotomous variable. People with a previous positive RT-PCR SARS-CoV-2 result that occurred more than 90 days after the current case will be classified as people with a previous SARS-CoV-2 infection [25].

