### Data Sources

This study will analyze the final datasets derived from the integration of several datasets provided by the Jakarta Provincial Health Office, Ministry of Health, and Social Security Agency on Health after April 2022 (Table 1). Variables such as ID number and date of birth will be used for the dataset linkage (Figure 2). From the New All Records (NAR) and Suspect and Probable (SUSPROB) datasets, symptomatic people with a positive or negative first RT-PCR test result within each of the periods of interest will be identified as cases or controls. Furthermore, people identified as cases will be linked to the entries in the REV POS dataset to extract the outcome of their disease course (Figure 2). People with incomplete data for ID number, date of birth, gender, swab collection date, PCR test result, domicile address, outcome, and date of death (if the case ends in death) will be excluded from further data linkage.

**Table 1 table1:** List source for merged datasets.

Name	Developer	Description	Variable identified
NAR^a^	Ministry of Health Republic of Indonesia	Record of all RT-PCR^b^ SARS-CoV-2 tests carried out by affiliated laboratories	Name ID number Date of birth Sex (male, female) Comorbidity Domicile address Laboratory name Reason for testing Swab collection date RT-PCR result confirmation date RT-PCR testing result
SUSPROB^c^	Jakarta Provincial Health Office	Record and follow-ups of all people with influenza-like illness or probable COVID-19	Name ID number Date of birth Sex (male, female) Comorbidity Domicile address Presence of influenza-like illness (fever, chill, cough, etc) Date of symptom onset Travel history Plan swab testing date Swab collection date RT-PCR testing result
REV POS	Jakarta Provincial Health Office	Records and follow-ups on all positive cases in Jakarta	Name ID number Date of birth Sex (male, female) Comorbidity Domicile address Date of swab collection Case severity (asymptomatic, mild, moderate, severe) Outcome (survived or death) Date of death
PCARE^d^ Vaksin	Social Security Agency on Health Indonesia (BPJS Kesehatan)	Record of all administered COVID-19 vaccines and their recipients	Name ID number Date of birth Sex (male, female) Domicile address Occupation or vaccination batch group (health workers, government officials, elderly, children, civilians) Name of health care facility/vaccination center Vaccination date Vaccination ticket number Vaccination dose Vaccine name Vaccine batch/lot number

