Misclassification of the exposure	During high levels of transmissibility, infection may occur soon after vaccination. Meanwhile, vaccines need time to confer an acceptable protective immune response.	High	Underestimate VE	All	Limit analysis only after vaccine performance has acceptable time to confer acceptable protection (eg, 14 days after the first or second dose, 7 days after third dose)	This study excludes infection that occurs <14 days after vaccination in the analysis of primary vaccine (first and second dose) and excludes events (eg, infection) that occur <7 days after vaccination in the analysis of booster vaccines. This measure will prevent underestimation of VE in the time when infection occurs during suboptimal immune response after vaccination.
Misclassification of the outcome	False positive and false negative	Small	Underestimate VE	All	Use only highly sensitive test (eg, RT-PCR^c^)	This study only includes RT-PCR SARS-CoV-2 results (see eligibility criteria) to control this bias
Spurious waning bias	This refers to an apparent VE reduction over time that does not reflect the decay of immunity over time but rather results from biases or confounding factors in the study design or analysis (eg, different variants, differences in exposure risk).	Small to large	Underestimate VE	All	Perform analysis for specific variant/period. Control difference in viral dynamic transmissibility over time. Perform stratification analysis by time since vaccination.	To prevent bias due to variants, this study conducts two sets of analyses (Delta and Omicron). To prevent bias due to differences in exposure risk over the periods of interest, we conducted matching case and control by calendar week of sample collection. To show VE waning, we perform stratification analysis by time since vaccination.

^a^VE: vaccine effectiveness.

^b^TND: test-negative design.

^c^RT-PCR: reverse transcription polymerase chain reaction.

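### Post-dose windows are counted to the test date, which may fall up to 10 days after symptom onset, so the exclusion of early illness claimed in Table 3 is not achieved; the bias is small in the main windows and material in the earliest strata

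*Protocol article*

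**What the plan says.** All the exposure timing in the protocol article refers to one date, the index RT-PCR test.

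- **Vaccination status** (Study Variables): "we will only consider the last vaccination data entry that happened before the patients’ index RT-PCR test date".
- **Main absolute VE windows** (Statistical Analysis): for the primary series, "we will include only vaccinated people with the last dose 1 or dose 2 vaccination date within 14-90 days"; for boosters, "with the last booster dose within 7-90 days before their index test date".
- **Relative VE** (Statistical Analysis): the booster window (7 to 90 days) and the two-dose comparator (90 days or more) are also counted back from the index test.
- **Waning subgroups** (Table 2): the first is "7-14 days between the last vaccination dose and index test date"; the other five use the same two dates.

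The illness may start well before that date. Study Participants admits people tested "due to symptoms of influenza-like illnesses within 10 days of the test date", and the primary outcome in Study Variables is "defined as a positive RT-PCR test within 10 days from the onset of influenza-like illness".

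Table 3 in the Discussion, in the row on misclassification of exposure, says what the windows are for: "This study excludes infection that occurs <14 days after vaccination in the analysis of primary vaccine (first and second dose", with a matching statement for events under 7 days after a booster. It adds that this prevents VE from being underestimated, and it rates this bias as high and as affecting all outcomes.

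Table 1 (Data Sources) lists "Date of symptom onset" among the SUSPROB variables.

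**The concern.** A window that opens 14 or 7 days after the dose is meant to keep out illness that began before the vaccine could act. It does so only if it is counted to the start of illness. Counted to a test that may come up to 10 days later, it lets in people who fell ill inside the period meant to be excluded. They enter the vaccinated group with the risk of the unvaccinated, which pulls VE down.

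Two things are at stake. First, the protocol states a safeguard that its own rule does not deliver. Second, the error is concentrated in people tested soon after a dose. VE by time since the last dose is a stated secondary objective, so the earliest points of that time course are the ones affected. A larger sample does not remove the error.

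**Working it through.** **1. The plan's own figure.** The only calculated figure is the sample size, about 5000 cases and 10,000 controls. It does not bear on the date problem, but its precision target of ±5% is a useful yardstick. With OR = 0.5 (VE 50%), 20% coverage in controls and two controls per case:

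- coverage in cases = 0.5 × 0.2 / (0.8 + 0.5 × 0.2) = 0.111
- variance term = 1/(0.111 × 0.889) + 1/(2 × 0.2 × 0.8) = 10.125 + 3.125 = 13.25
- cases = (1.96 × 0.5 / 0.05)² × 13.25 ≈ 5,090, or about 15,270 in total

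This is the largest value over the stated ranges of VE and coverage, and it reproduces the plan's figure within 3%.

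**2. Date arithmetic, from the protocol alone.** Onset day after dose = test day − delay, with delay 0 to 10 days.

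| Dose | Window opens (test day) | Earliest admissible onset | Test days affected | First test day that is safe without an onset date |
|---|---|---|---|---|
| 1 or 2 | 14 | 14 − 10 = day 4 | 14-23 | 24 |
| Booster | 7 | 7 − 10 = day −3 | 7-16 | 17 |

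Infection precedes onset, so the gap against Table 3, which speaks of infection, is wider still.

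**3. Size, on assumptions.** The article gives no delays, no spread of tests and no protection curve. Assumed here:

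- test days spread evenly over each window
- no protection before day 14 (dose 1 or 2) or day 7 (booster), full protection after
- true VE 70%
- delay either uniform on 0-10 days (mean 5) or truncated geometric (mean 1.87)

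Let f be the share of vaccinated test-negatives whose onset fell before the cut-off. Then observed OR = f × 1 + (1 − f)(1 − VE), so **observed VE = VE × (1 − f)** and the bias is f × VE.

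Where a window runs at least 10 days past its opening, f = mean delay / number of days in the window. The 7-14 day subgroup is shorter, so it is counted directly. With uniform delay, test days 7 to 14 have 10, 9, 8, 7, 6, 5, 4 and 3 contaminating delays out of 11 each, so f = 52/88.

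| Stratum | f, mean delay 1.87 | f, mean delay 5 | 70% reads |
|---|---|---|---|
| Dose 1/2, 14-90 days | 1.87/77 = 2.4% | 5/77 = 6.5% | 68% to 65% |
| Booster, 7-90 days | 1.87/84 = 2.2% | 5/84 = 6.0% | 68% to 66% |
| Dose 1/2, 14-28 days | 1.87/15 = 12.5% | 5/15 = 33.3% | 61% to 47% |
| Booster, 7-14 days | 23.1% | 52/88 = 59.1% | 54% to 29% |
| Booster, if follow-up is only 7-30 days | 1.87/24 = 7.8% | 5/24 = 20.8% | 65% to 55% |

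Onset before the booster itself accounts for 0.1-0.6% of the 7-90 day window and 0.6-6.8% of the 7-14 day subgroup.

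**4. Short follow-up in the Omicron wave.** The national booster programme is dated January 2022, and the Omicron period runs from January 1 to April 2, 2022 (92 days). If booster and test dates were both uniform over those days (assumption), an interval of t days has weight 92 − t. The weights over days 7-90 sum to 3,654. With uniform delay the contaminated weight is Σ (10 − j)/11 × (85 − j) for j = 0 to 9, which is 410, so f = 410/3,654 = 11.2% and 70% reads 62%. With mean delay 1.87, f = 4.3% and 70% reads 67%.

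**5. Where it stops.** The last affected test day is 23 for dose 1 or 2 and 16 for boosters. Table 2 subgroups 3 to 6 (28 days onward) contain no such test days.

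**The case against.** **The test date is a declared choice.** Study Objectives lists VE by vaccination status at the time of the RT-PCR test, and the outcome is defined through the positive test. On that reading a positive test under 14 days after the dose is indeed excluded. This confirms which date is meant, but it does not remove the bias that Table 3 says is controlled.

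**The main result hardly moves.** This stands. With even spread, a true VE of 70% loses about 2 to 5 points, inside the planned ±5%. A reader might infer that the headline estimates are badly biased; the arithmetic does not support that.

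**Waning can still be read.** This stands from day 28 onward. A reader might infer that the whole waning analysis is distorted, but only subgroups 1 and 2 are. For dose 1 or 2, subgroup 1 already lies before the 14-day point.

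**The large figures rest on assumptions, and ill people may put off vaccination.** Both stand. Onset before a booster is an edge case. Most of the effect comes from onset after the dose but before the cut-off.

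**Controls are misdated too.** True, but this does not cancel. Vaccinated people who are not yet protected have an odds ratio near 1 and are pooled with the protected.

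**Onset date may be incomplete.** Table 1 lists it for SUSPROB and not for NAR, the other source of cases and controls, and it is not among the fields whose absence leads to exclusion. This stands, and it raises the cost of the fix. The 10-day eligibility rule nevertheless already needs that date.

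**Conclusion.** The concern holds in a limited form. That the rule admits onset from day 4 after dose 1 or 2, and from 3 days before a booster, follows from the protocol's own dates. The exclusion stated in Table 3 is therefore not achieved, and its claim to prevent underestimation is too strong.

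The size is less certain, because delay, spread of tests and early protection are all assumed. On those assumptions the main windows are a minor matter. The 14-28 day subgroup for dose 1 or 2 and the 7-14 day subgroup for boosters are materially too low. Recent boosters in the Omicron wave lie between: at the upper end of the assumed delays the loss is about 8 points, more than the planned precision.

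This should be corrected before the early time-since-dose results are interpreted. It does not invalidate the main estimates or the later waning subgroups.

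**What to change.** - Count vaccination status, the absolute and relative VE windows and the Table 2 intervals from the last dose to symptom onset, for cases and controls alike. Take the last dose before onset rather than before the test.
- Keep the index test date for assigning the wave and the calendar week.
- Report the test-date version as a sensitivity analysis.
- Align Study Objectives, Study Variables, Statistical Analysis, Table 2 and the exposure row of Table 3.

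**Cost.** The code change is one date variable, but a secondary objective must also be reworded. Records without an onset date leave the onset-based analysis, so report completeness separately for cases and controls.

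**If completeness is poor.** Keep the test date, add a sensitivity analysis with windows that open at day 24 (dose 1 or 2) and day 17 (booster), interpret subgroups 1 and 2 with caution, and withdraw the Table 3 statement that underestimation is prevented.
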